### Sample size rationale/number of patients

A sample size estimation was performed using data of a post-hoc analysis of the COMPASS trial [18]. In this trial at 1 year, LITA-to-LAD graft occlusion occurred in 7.3% (21/289) of skeletonized and in 3.4% (25/725) of pedicled grafts (the COMPASS trial did not provide 2-year results). In addition, within 2 years, 5 of 1014 patients died. Rounding up this numbers, we consider event rates of 4% (pedicled) versus 8% (skeletonized) at 2 years as a realistic, conservative scenario for our study. In order to detect this difference of 4% (corresponding to a hazard ratio of 0.49), as statistically significant with a two-sample log-rank test, a sample size of 558 patients in each treatment group is needed, assuming a type I error of 0.05 (alpha = 5%) and a power of 0.8 (beta = 20%), requiring 62 events (death or LITA occlusion) in total. To account for dropouts and withdrawals, we increased the sample size to 675 patients in each group, resulting in a total sample size of 1350 patients for the trial.

### Study population

The following populations will be used for statistical analysis: (i) The intention-to-treat population, which comprises all individuals who are randomized to 1 of the arms of the HARVITA trial, regardless of adherence, treatment or protocol deviations; (ii) modified intention-to-treat population, which includes individuals who are randomized, undergo the surgical procedure and have a LITA graft anastomosed to the LAD.

## DATA ANALYSIS

### Demographic and baseline characteristics

A flow chart will be produced, showing the number of patients screened, excluded, randomized, receiving surgery and having follow-up. Baseline demographic data will be presented as absolute numbers with percentages for categorical variables and as mean+/- standard deviation or median (interquartile range) for continuous variables.

### Efficacy analysis

The primary end point of LITA graft occlusion-free survival will be compared between the 2 treatment groups using Kaplan–Meier graphs and a centre-stratified two-sample log-rank test. In addition, Cox proportional hazards regression analysis adjusting for clinically relevant confounders, will be performed. Hazard ratios and their 95% confidence intervals will be estimated.

The primary efficacy hypotheses will thus be formulated as:H_0_: hazard ratio_skeletonized vs pedicled_ = 1H_1_: hazard ratio_skeletonized vs pedicled_ ≠ 1

The primary efficacy analysis will be performed in the modified intention-to-treat population population.

MACE-free survival and other secondary end points that follow the time-to-event format will be analysed with Kaplan–Meier test,log-rank test and Cox proportional hazards regression analysis. Categorical end points will be compared between treatment groups using the χ^2^ test. *P*-values < 0.05 will be considered statistically significant; however, formal significance testing will be applied to the primary hypothesis only. Statistical tests for secondary end points will be applied in a descriptive manner only.

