### Randomization, stratification and enrolment

All patients having a planned isolated CABG procedure are screened according to the inclusion and exclusion criteria. Those patients who are eligible and have given informed consent will be randomized to 1 of the 2 treatment arms (skeletonized or pedicled harvesting technique).

Patients will be randomized in a 1:1 fashion. Permuted block randomization with variable block sizes and stratification by centre will be performed with a web-based randomization system in order to achieve an equal distribution in both groups. Log will be held for all screened patients with reasons for inclusion and exclusion.

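### Centre stratifies randomisation and the primary log-rank test, but is not stated for the Cox model giving the primary hazard ratio and CI, nor for the secondary tests; the effect is small and the fix is cheap

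*Protocol article*

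**What the plan says.** Protocol article, Randomization, stratification and enrolment: "Patients will be randomized in a 1:1 fashion", and "Permuted block randomization with variable block sizes and stratification by centre will be performed with a web-based randomization system". Centre is the only stratification factor named.

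Protocol article, Efficacy analysis: the primary end point is compared "using Kaplan–Meier graphs and a centre-stratified two-sample log-rank test". In addition there is "Cox proportional hazards regression analysis adjusting for clinically relevant confounders", and "Hazard ratios and their 95% confidence intervals will be estimated". The confounders are not listed, and centre is neither included nor excluded. The null and alternative hypotheses are written in terms of the hazard ratio.

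The same section names log-rank and Cox analyses for MACE-free survival and the other time-to-event outcomes, this time without centre. For the remaining outcomes, "Categorical end points will be compared between treatment groups using the" χ² test. It reserves formal testing for the primary hypothesis and treats the secondary tests as descriptive.

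**The concern.** An analysis should normally reflect the factor by which randomisation was stratified. The plan accepts this for its main test and then does not state it for anything else. One log-rank test is labelled centre-stratified and the next is not, so the natural reading is that they differ. An ordinary χ² test is unstratified by definition.

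Centre differences are plausible here. The harvesting device follows each centre's habit, postoperative treatment follows local standards, and CT scans are acquired and first read locally.

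Two things could be at stake. First, the p-value for the one formal hypothesis (stratified) and the hazard ratio with its CI (possibly unstratified) may point different ways. Second, the secondary comparisons may give up a little precision or power that the design has already paid for.

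**Working it through.** **The plan's own figures.** Inputs from the sample size section: 4% and 8% at 2 years, alpha 0.05, power 0.80. (1.960 + 0.842)² = 7.849.
- Hazard ratio = ln(0.96)/ln(0.92) = 0.490, as stated.
- Freedman: 7.849 × [(1 + 0.4896)/(1 − 0.4896)]² = 66.8, so 67 events; 67/(0.04 + 0.08) = 558 per arm, as stated.
- Schoenfeld: 4 × 7.849/[ln(0.4896)]² = 61.5, so 62 events, as stated.

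The 558 and the 62 thus come from different formulas. That is a separate matter, and neither figure depends on centre.

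**Time-to-event outcomes, by simulation.** N = 2 × 558 = 1,116, balanced 1:1 within centres of unequal size, 2 years of follow-up, 1,500 trials per scenario. Either 4% against 8% (true log hazard ratio, skeletonized to pedicled, −ln 0.4896 = 0.714) or 6% in both arms. The document gives neither the number of centres nor their heterogeneity; 10 or 20 centres and a between-centre SD of the log-hazard of 0, 0.5 or 1.0 are assumptions. The Cox models contain treatment only. Each cell gives unstratified / centre-stratified under 4% against 8%; power is that of the log-rank test.

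| Centres, SD | Mean log HR | CI width ratio | Power, % |
|---|---|---|---|
| 10, 0 | 0.726 / 0.725 | 0.9999 | 81.3 / 81.2 |
| 10, 0.5 | 0.716 / 0.720 | 0.9998 | 78.9 / 79.3 |
| 10, 1.0 | 0.712 / 0.732 | 0.9996 | 73.7 / 74.9 |
| 20, 0 | 0.716 / 0.716 | 0.9998 | 80.1 / 79.7 |
| 20, 0.5 | 0.729 / 0.735 | 0.9997 | 81.7 / 81.8 |
| 20, 1.0 | 0.718 / 0.741 | 0.9992 | 76.0 / 77.9 |

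Interval coverage over all 12 scenarios was 94.3% to 96.1% without centre and 94.3% to 95.9% with it.

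Share of trials in which the Cox Wald test and the centre-stratified log-rank test fell on opposite sides of 0.05 (range over 10 and 20 centres, with and without a treatment effect):

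| SD | Unstratified Cox | Stratified Cox |
|---|---|---|
| 0 | 0.1% to 0.9% | 0.1% to 0.8% |
| 0.5 | 0.5% to 1.2% | 0.3% to 0.5% |
| 1.0 | 1.3% to 3.3% | 0.3% to 1.2% |

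Three cautions apply.
- The unstratified means at SD 1.0 lie close to the simulated 0.714, so the gap of 0.741 − 0.718 = 0.023 is a difference between two estimators, not proof that the smaller one is the worse.
- At SD 1.0 with no treatment effect, the unstratified log-rank rejected in 4.9% and 4.5% of trials and the stratified in 6.1% and 5.4%. The simulation error there is about √(0.05 × 0.95/1,500) = 0.6 points, so the power gain of 1.2 to 1.9 points is approximate.
- The primary log-rank test is already stratified, so its own power is untouched. The loss applies to an unstratified secondary analysis or to a reading through the Cox result.

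**Categorical outcomes.** The share of the outcome variance that lies between centres is about p(1 − p) × SD², with SD on the log-odds scale. For p = 12%, SD 0.5: 0.1056 × 0.25 = 2.6%, hence a standard error about 1.3% too large. Simulation of the risk difference under no effect (about 560 per arm, 10 to 20 centres, 6,000 trials per setting) gave these pooled to within-centre ratios:
- 12%, SD 0.5: 0.01999/0.01975 = 1.012
- 12%, SD 0.8: 0.02086/0.02014 = 1.036
- 4%, SD 0.5: 0.01226/0.01220 = 1.005
- 4%, SD 0.8: 0.01317/0.01296 = 1.016

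At 12% the type I error was 4.1% to 4.6%, on the conservative side. The rates and SDs are assumptions.

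**The case against.** The strongest reply is that this is a condensed article. Covariates and strata terms are commonly left to the full protocol or SAP, and the one formal test already carries the stratification factor. This stands in part. For the Cox model, a reader might infer that centre is left out; the text supports only that it is not stated, since it could be among the unlisted covariates. For the χ² test, though, the article does name an unstratified method.

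A reader might also infer that the hazard-ratio CIs are too wide. They are not. The standard-error excess shown above belongs to a binary risk difference. In a Cox model, omitting a prognostic factor mainly pulls the estimate towards zero and leaves the interval width alone. Nor does the excess extend to every secondary outcome: MACE-free survival is analysed as time to event.

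Finally, disagreement between test and estimate is rare. Adjustment for confounders can itself separate the Cox result from the log-rank test, and a stratified Cox model does not abolish disagreement. All of this stands, and it limits the point to a minor one.

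**Conclusion.** The point holds as a minor improvement. The plan does not align the primary hazard ratio and CI with the centre-stratified primary test, and it names ordinary tests for the secondary end points although the design is stratified.

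With no or moderate centre differences the consequence for time-to-event outcomes is negligible. Only under strong assumed heterogeneity does it become visible, as a slightly smaller log hazard ratio, 1 to 2 points of log-rank power, and somewhat more frequent disagreement with the primary test. For categorical outcomes the unstratified analysis is mildly conservative, and no formal conclusion rests on it. The validity of the primary test is not in question. All sizes rest on assumed centre numbers, heterogeneity and, for categorical outcomes, event rates.

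**What to change.** - Report the primary hazard ratio and 95% CI from a Cox model with treatment only, stratified by centre, so that it matches the stratified log-rank test.
- Keep the confounder-adjusted Cox model as supportive, also stratified by centre.
- Use centre-stratified log-rank and Cox analyses for the secondary time-to-event outcomes, and a Cochran–Mantel–Haenszel test stratified by centre in place of χ² for the categorical ones.
- If the full protocol or SAP already says this, confirm it and align the wording.

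The cost is a few sentences and a strata term; centre is already recorded for randomisation. The one real downside is that very small centres contribute little or nothing to a stratified analysis, so a rule for pooling them must be fixed before unblinding and applied equally to the test and the estimate.

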### Safety analysis

Safety variables will be summarized using descriptive statistics and tabulated by treatment group.

A safety monitoring committee comprised of 3 independent consultants (2 consultants in cardiac surgery, 1 consultant in cardiology) will meet annually and inspect the follow-up data. The primary safety outcome composed of death, myocardial infarction and stroke, as well as the secondary safety outcome, composed of periprocedural major complications (reoperation due to bleeding, perioperative myocardial infarction, dialysis, tracheostomy, stroke and deep sternal wound infections) will be compared. In case of a greater than 10% difference between the 2 treatment groups, the safety monitoring committee, together with the trial steering committee, will temporarily pause the randomization of further patients until a final decision is made. This final decision could be either the early termination of the trial, a change in the study protocol or the continuation of the trial.

### Software

All statistical analyses will be performed with SPSS Version 28 (IBM Corporation, Armonk, NY, USA), MedCalc Version 19.4, GraphPad Prism version 9.0. and R 3.2.2 (The R Foundation for Scientific Computing, Vienna, Austria).

### Ethics

Permission for this study was obtained from the local institutional review board on 1 December 2023 (Medical University of Innsbruck) (EK Nr: 1135/2023). All participating centres will apply for approval of the study protocol from their local institutional review board before proceeding with enrolling patients in the trial.

### Registration

The HARVITA trial is registered at ClinicalTrials.gov (NCT05931783).

## Data Availability

The data underlying this study will be available upon request from the corresponding author.

## ABBREVIATIONS

CABG: Coronary artery bypass grafting
CAG: Coronary angiography
cCTA: Coronary computed tomography angiography
CT: Computed tomography
ITA: Internal thoracic artery
LAD: Left anterior descending artery
LITA: Left internal thoracic artery
MACE: Major adverse cardiac events
RA: Radial artery
RITA: Right internal thoracic artery
SVG: Saphenous vein graft
